#### Assessment of quality of life (AQoL-8D)

The AQoL-8D will be used to assess health related quality of life [33]. It is commonly used to calculate utility scores before and after intervention for use in economic evaluation studies. The AQoL-8D can be completed in 5 minutes and is comprised of 35 items from which eight dimensions and two ‘super-dimensions’ are derived. The 35 items may be reduced to a single utility score using the AQoL-8D algorithm. AQoL-8D score ranges from full health (1.00) to health states worse than death (− 0.04) [34]. In addition, the algorithm produces an index number for each of the eight dimensions and for the two ‘superdimensions’, ‘Physical super-dimension’ (PSD; independent living, pain, senses) and ‘Mental super-dimension’ (MSD; mental health, happiness, coping, relationships, self-worth). The AQoL-8D has been shown to have good criterion validity, with Cronbach’s Alpha of 0.97.

### Statistical analysis

#### Analysis plan

Primary analyses will be undertaken on an intent-to-treat basis, including all participants as randomised, regardless of treatment actually received or withdrawal from the study. Likelihood based methods (mixed-model repeated measures [MMRM]) methods will be used to analyse change in the primary outcome measure (SIDAS). An a priori planned comparison of change from baseline to the post-intervention endpoint (6 weeks) will be used to test the primary hypothesis. An unstructured variance–covariance matrix will be used to accommodate relationships between observations at different occasions. The stratification factor of gender will be included in these models and variables found to be substantially imbalanced (equating to a moderate effect size) between groups post-randomisation will be tentatively included but not retained to evaluate the robustness of conclusions reached. Similar analyses of continuous/scaled secondary measures will assess differential change due to intervention arm. Mathematical transformation or categorisation of raw scores into ordered or dichotomous classes may be undertaken to meet distributional assumptions and address any violation of assumptions attributable to outliers. MMRM assumes data are missing at random [35, 36]. As this assumption cannot be substantiated from observed data, sensitivity analyses will be undertaken to evaluate effects of missing data and the robustness of the trial’s conclusions. As appropriate, these will be based on plausible models of missingness informed, as much as possible, by the experience of those working closely with participants.

For dichotomous outcomes such as caseness, a comparable generalized mixed modelling approach will be used. Number needed to treat [37] to avoid high risk of suicidal behaviour will be derived from the SIDAS using a cut-off score of 21 [24]. Number needed to treat to avoid moderate depression will be derived from the PHQ-9 using a cut-off score of 10 [38]. Separate analyses will incorporate 6-month follow up data. At this stage it will be possible to estimate post-intervention change in the active group and also to estimate change in the wait-list group after use of the app; however, comparison with an untreated sample will not be possible. All tests of treatment effects will be conducted using a two-sided alpha level of 0.05 and 95% confidence intervals.

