### Randomisation

Randomisation of participants will occur with equal probability for both groups. Participants will be stratified based on gender (male/female) and severity of suicidal thoughts calculated from the SIDAS [24], using a cut-off score of 21 (subthreshold/high risk). Randomisation will be carried out at the Black Dog Institute by the trial manager using automated randomisation software for block randomisation (four per block). Participants were aware of allocation as they were provided the tablet with the app if randomised to the iBobbly group.

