#### Sample size and power calculations

Power to detect change in ideation is based on the expected effect of the intervention at the 6-week time point on the primary outcome measure (SIDAS) after completion of the intervention as delivered by the app (6 weeks post baseline). Expected effects were based on the findings from a recent Dutch trial using a modified CBT website in the general population [39] which reported an effect size of 0.28 (Cohen’s d). A smaller effect than this on suicidal ideation would mean the app would be of limited interest as an intervention. To be able to detect this effect size, assuming a correlation between baseline and post-intervention measures of 0.5, including an expected drop-out rate of 30%, 289 participants, yielding complete data from 202 people, will be needed in each condition (with alpha = 0.05 and power of 0.80). This will also result in good precision, yielding confidence intervals of width approximately ± 0.20 for the effect size. US data show that 33.4% of adolescents with suicidal ideation also report plans [40]. Assuming this rate of plan reporting in the control condition, a reduction of plans under the active intervention to 20.5% (relative risk 0.61) would be required to maintain 80% power using Fisher’s exact test. While the study is not explicitly powered to detect this outcome, it is plausible that reduction in rates of plan-making may be detected with the target sample size. It may be feasible to determine when plans were made, allowing the testing of hypotheses regarding plans using more clinically informative methods such as survival analysis.

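### The primary SIDAS contrast is a comparison of change with no stated baseline adjustment; on the protocol's own inputs, adjusting would raise power from about 83% to about 90% at no extra data cost

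*Protocol article*

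**What the plan says.** The Analysis plan section of the protocol article sets the primary test: "An a priori planned comparison of change from baseline to the post-intervention endpoint (6 weeks) will be used to test the primary hypothesis". The analysis is a likelihood-based MMRM on an intent-to-treat basis. On covariance it says: "An unstructured variance–covariance matrix will be used to accommodate relationships between observations at different occasions". On covariates it says: "The stratification factor of gender will be included in these models". Other variables that turn out imbalanced are added only as a robustness check and are not kept. Data from 6 months are reserved for separate analyses.

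The Randomisation section uses two stratification factors: "Participants will be stratified based on gender (male/female) and severity of suicidal thoughts calculated from the SIDAS", with a cut-off of 21. Only gender is carried into the model. Nothing in the article names baseline SIDAS as a covariate or says that the arms share a baseline mean.

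The Sample size section takes d = 0.28 from an earlier trial of a web-based intervention, "assuming a correlation between baseline and post-intervention measures of 0.5", 30% dropout, alpha 0.05 and power 0.80. It arrives at 202 complete and 289 randomised per arm, with precision of about ±0.20 on the effect size.

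**The concern.** A difference in change subtracts the whole of the baseline value. Unless the correlation between baseline and outcome is very high, this over-corrects: it removes some between-person variance and adds back noise from the baseline measurement. At r = 0.5 the two cancel exactly among completers, so measuring SIDAS at baseline brings no precision there. Adjustment by regression, or by a model that gives both arms one baseline mean, subtracts only the part of baseline that predicts the outcome. It is more precise at every r below 1.

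The stake is power for the primary outcome. The article says that an effect smaller than 0.28 would be of limited interest, so power at 0.28 is the figure that matters. The Community consultation section reports difficulty with recruitment, so precision may be scarce.

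**Working it through.** **Inputs.** From Sample size and power calculations: d = 0.28, r = 0.5, 202 complete and 289 randomised per arm. From Analysis plan: two-sided alpha 0.05. Assumptions: outcome SD = 1 at both occasions (so d is in outcome-SD units), random dropout, and baseline means free in each arm under the plan.

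**1. Reproducing the plan's figure.** The SD of change is √(2(1 − r)) = √(2 × 0.5) = 1.000. A two-sample t calculation for d = 0.28 at 80% power gives 202 per arm (201 by normal approximation), and 202 / 0.70 = 288.6, so 289. The confidence interval half-width is 1.96 × √(2/202) = 0.195, matching the stated ±0.20. All three figures reproduce.

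**2. Completers only.**
- Change: SD 1.000, power at 202 per arm 80.2% (noncentral t).
- Baseline-adjusted: SD √(1 − r²) = √0.75 = 0.866, power 90.0%, half-width 1.96 × √(0.75 × 2/202) = 0.169.
- Information lost by using change: 1 − 0.75/1.00 = 25%.
- Completers needed for 80% power with adjustment: 152 per arm (t), or 218 randomised.

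**3. The planned likelihood model.** It also uses the 289 − 202 = 87 participants per arm with baseline data only. With baseline means free, the variance per arm of the estimated mean change is

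(1 − r²)/202 + (1 − r)²/289.

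With a common baseline mean, or with baseline as a covariate, only the first term remains. At r = 0.5:
- Planned: 0.75/202 + 0.25/289 = 0.003713 + 0.000865 = 0.004578. Power = Φ(0.28/√(2 × 0.004578) − 1.96) = Φ(0.966) = 83.3%.
- Adjusted: 0.003713. Power = Φ(0.28/√(2 × 0.003713) − 1.96) = Φ(1.289) = 90.1%.
- Information lost: 1 − 0.003713/0.004578 = 18.9%.

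A simulation of 20,000 trials gave 80.9% (change, completers), 83.2% (planned model) and 90.2% (adjusted).

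**4. Other correlations**, by the same formulas. These values are illustrative; the protocol gives only 0.5.

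| r | Planned model | Adjusted |
|---|---|---|
| 0.3 | 71% | 84% |
| 0.4 | 77% | 87% |
| 0.5 | 83% | 90% |
| 0.6 | 90% | 94% |
| 0.7 | 96% | 98% |

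At r = 0.45 the planned variance is 0.7975/202 + 0.3025/289 = 0.004995, which gives 80.0% power. Below that the stated target is missed. The planned contrast becomes less precise than ignoring baseline when (1 − r)²/289 exceeds r²/202, that is, when r is below 1/(1 + √(289/202)) = 0.455.

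**The case against.** **Free baseline means are not stated.** A model with a common baseline mean can also report a change from baseline, and a condensed article may leave the parameterisation to a fuller plan. This stands as a limit on certainty. Free means are the plain reading of a change contrast with only gender retained, but if a constraint or covariate was intended, the design already has about 90% power and the text needs only to say so.

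**The sample size does not settle the model.** A reader might infer from 202 per arm that a change-score test must be planned. It cannot show that: at r = 0.5 the change-score and post-score calculations give the same number, and a simple formula alongside a more efficient analysis is ordinary caution.

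**The loss is easily overstated.** A reader might conclude that baseline contributes nothing, that the gain is 10 points, or that power fails once r drops below 0.5. Those statements hold for completers only. The planned likelihood analysis also uses baseline-only participants, so the gain at r = 0.5 is about 7 points and the threshold for missing 80% is about 0.45. Stratifying on SIDAS severity also limits baseline imbalance and narrows the gap slightly: a simulation with stratified blocks gave about 82% rather than 80% for change in completers, against 90% adjusted.

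**Low correlations are hypothetical.** The protocol gives no reason to expect 0.3 or 0.4. If 0.28 had been standardised on change, power would not fall with r in completers.

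**Nothing is invalid.** Under randomisation the change contrast is unbiased, holds its type I error, and meets the 80% target on the stated inputs. This is correct and sets the weight of the point.

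**Conclusion.** The point holds as an efficiency improvement. On the plain reading, the planned contrast has about 83% power against about 90% with baseline adjustment, a loss of about 19% of the information on the primary outcome. Put as risk, a true effect of 0.28 would be missed about 17% of the time instead of 10%. If r were 0.4 or 0.3, the figures would be about 77% or 71%, against 87% or 84%.

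This rests on d = 0.28 being in outcome-SD units, r = 0.5, equal SDs at both occasions, 202 of 289 completing per arm with dropout at random, and free baseline means. The last is inferred from the text. The documents do not support a claim that the planned test is wrong, biased or underpowered on its own inputs.

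**What to change.** State in the Analysis plan that the primary estimate is the arm difference in mean SIDAS at 6 weeks, from the planned unstructured MMRM with baseline means constrained to be equal across arms. Do the same for each scaled secondary outcome with its own baseline.

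Adjusting for continuous baseline SIDAS as a covariate gives essentially the same precision. However, with only post-baseline values as the response, participants with no follow-up drop out of the model, which sits badly with the commitment to include everyone as randomised. The common-baseline-mean form keeps them and is the cleaner choice. Either form also largely takes up the SIDAS severity stratification factor, which the model now omits.

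The cost is one sentence. Baseline SIDAS is already needed for stratification, and the covariance structure, analysis population and sample size can stay as they are. The Trial status section says the article was submitted before the code was broken or any data analysed, so a change made at that stage would be prespecified. If the model already includes a common baseline mean or baseline covariate, say so, and note that the 202 per arm is then conservative.

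### Randomisation is stratified by gender and SIDAS severity but the models carry only gender, so the primary change contrast, as described, is mildly conservative

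*Protocol article*

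**What the plan says.** The Randomisation section names two stratification factors: "Participants will be stratified based on gender (male/female) and severity of suicidal thoughts calculated from the SIDAS". The SIDAS cut-off is 21, allocation is 1:1 and blocks have size four.

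The Analysis plan specifies a mixed model for repeated measures with an unstructured covariance and names one design factor as a model term: "The stratification factor of gender will be included in these models". Other variables have a conditional route only: "variables found to be substantially imbalanced (equating to a moderate effect size) between groups post-randomisation will be tentatively included but not retained". The stated purpose of that route is to check robustness.

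The primary contrast is given as follows: "An a priori planned comparison of change from baseline to the post-intervention endpoint (6 weeks) will be used to test the primary hypothesis". On the level of the tests: "All tests of treatment effects will be conducted using a two-sided alpha level of 0.05", with 95% confidence intervals. Nowhere does the article say that baseline SIDAS is a covariate, or that the arms share a common baseline mean.

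**The concern.** Stratified blocks balance the arms on severity. If severity predicts the quantity analysed, that balance reduces the true sampling variation of the treatment difference. A model without the stratum does not see the reduction. It leaves the between-stratum variation in the residual and reports a standard error that is too large.

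Here the omitted factor is a dichotomised form of the primary outcome at baseline. Change from baseline is correlated with baseline, so the stratum predicts change. The nominal 5% test and 95% interval would then not have their stated level, and precision that the design has already secured would go unused. The article does not leave the covariates open for a later document: it states a rule, and the rule keeps one design factor and omits the other.

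**Working it through.** **Inputs from the protocol.** Effect size d = 0.28, baseline to 6-week correlation ρ = 0.5, two-sided alpha 0.05, power 0.80, dropout 30%, 202 completers and 289 randomised per arm (Sample size and power calculations); strata and block size (Randomisation).

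**Assumption.** The share p of participants with SIDAS of 21 or more is not given. It is varied from 10% to 50%.

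**Step 1: reproduce the plan's sample size.** With unit SD at each occasion, the SD of change is √(2(1 − ρ)) = √(2 × 0.5) = 1. The noncentral t calculation for d = 0.28 gives 202 per arm (power 0.8016), and 202/0.70 = 288.6, so 289. A baseline-adjusted analysis, with SD √(1 − 0.5²) = 0.866, would need only 151. The stated size is therefore that of a change contrast not adjusted for baseline.

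**Step 2: how much of the change the stratum explains.** Corr(change, baseline) = −√((1 − ρ)/2) = −0.5 at ρ = 0.5, so baseline explains 25% of the variance of change. Dichotomising a normal baseline at its upper p-quantile z keeps the fraction φ(z)²/(p(1 − p)). Hence

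R² = ((1 − ρ)/2) × φ(z)²/(p(1 − p)).

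For p = 0.3: z = 0.524, φ(z) = 0.348, the fraction is 0.1209/0.21 = 0.576, and R² = 0.25 × 0.576 = 0.144.

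**Step 3: effect on the test.** True SE / model SE = √(1 − R²). Actual alpha = 2(1 − Φ(1.96/√(1 − R²))). With 202 per arm the standardised effect is 0.28 × √101 = 2.814. Power as written is Φ((2.814 − 1.96)/√(1 − R²)). Power with the stratum in the model is Φ(2.814/√(1 − R²) − 1.96).

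| p | R² | true/model SE | actual alpha | power as written | power with severity |
|---|---|---|---|---|---|
| 10% | 0.086 | 0.956 | 4.0% | 81.4% | 83.7% |
| 20% | 0.122 | 0.937 | 3.6% | 81.9% | 85.2% |
| 30% | 0.144 | 0.925 | 3.4% | 82.2% | 86.0% |
| 50% | 0.159 | 0.917 | 3.3% | 82.4% | 86.6% |

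The model SE is too large by 1/0.956 − 1 = 5% up to 1/0.917 − 1 = 9%. With ρ varied from 0.3 to 0.7, the actual alpha ranges from 2.6% to 4.4%.

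**Step 4: simulation.** Permuted blocks of four within gender by severity, a two-occasion likelihood model with unstructured covariance, 5,000 trials per setting, ρ = 0.5. Settings included 30% dropout and SIDAS-like scores floored on 0–50.

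- Gender only, as written: type I error 3.1–4.2%.
- Gender plus severity by occasion: 4.5–5.5%.
- Gender only, with baseline means constrained equal (equivalent to baseline adjustment): 4.6–5.2%.

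The Monte Carlo standard error is about √(0.05 × 0.95/5000) = 0.3 percentage points. A separate simulation at 202 per arm without dropout gave a type I error of about 3.0–4.2% as written and 4.6–5.6% with severity. Power rose from 81–83% to 84–87%, a gain of about 2–5 points.

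**Step 5: can the conditional route bring severity in?** Severity is balanced by design, so it would not qualify as imbalanced. A variable that did qualify would not be retained.

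**The case against.** **Baseline SIDAS is already an occasion in the model.** This does not remove the problem. With free arm-by-occasion means and an unstructured covariance, the complete-data contrast is simply the difference in mean change, which still depends on the stratum.

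**The result depends on the parameterisation.** This stands. If baseline SIDAS is a covariate, or baseline means are constrained equal, the effect on the primary outcome disappears even with gender alone. The analysis plan, which is not shown, may specify this. The article states neither, and its sample size matches the unadjusted contrast.

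**Nothing is lost against the plan.** This also stands. A reader might infer that the trial is underpowered or its result biased. The documents do not support that: power as written is 81–82% in closed form against a stated 80%, and the error is on the conservative side.

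**Dichotomous outcomes behave differently.** A reader might infer that their intervals are also too wide and that severity by occasion belongs in every model. Neither follows. On the log-odds scale, adjusting for a prognostic factor raises the standard error: with 202 per arm and ρ = 0.5, simulation gave 0.251 rising to 0.263 (20% high) and 0.204 rising to 0.216 (40% high). The unadjusted test was still conservative, at about 3.6%. For SIDAS of 21 or more with baseline as an occasion, the baseline outcome is the stratum itself. Severity by occasion then predicts it perfectly and the treatment contrast cannot be estimated. Continuous baseline SIDAS fails there for the same reason.

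**The imbalance clause is a robustness check.** Correct. It was not written to repair standard errors, and there is no reason to delete it.

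**Conclusion.** The mismatch between the Randomisation section and the Analysis plan is real, and its consequence is modest. For the primary contrast as described, the standard error is about 5–9% too large, the 5% test runs at about 3–4%, and about 2–5 points of power are forgone. These figures rest on ρ = 0.5 from the protocol, an assumed 10–50% in the high stratum, free arm means at each occasion and no use of baseline SIDAS as a covariate or constraint.

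For the scaled secondary outcomes the direction is the same, but the size depends on how strongly severity predicts change in each, which the document does not give. An assumed correlation of 0.6 between a secondary scale and baseline SIDAS gave a type I error of 4.2–4.5%, which is a small effect. The point is worth correcting because the fix is nearly free. It does not threaten the validity of a positive result.

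**What to change.** In the Analysis plan:

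1. State that the SIDAS severity stratum, with its interaction with occasion, enters the primary and scaled secondary models alongside gender. The interaction is needed because a main effect alone barely alters a change contrast.
2. For the primary outcome, allow as an alternative continuous baseline SIDAS as a covariate, or baseline means constrained equal across arms.
3. For dichotomous outcomes, include severity as a covariate in models of post-baseline occasions only. The gain there is a correct test level and power, not a narrower log-odds interval.
4. Keep the imbalance-triggered check as a sensitivity analysis.

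The cost is wording. The stratum is known for every randomised participant, and no further data or change in sample size is needed.

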**Methods/design:**

This is a two-arm randomised controlled trial that will compare iBobbly to a wait-list control condition. The trial aims to recruit Aboriginal and Torres Strait Islander participants aged 16 years and over to test iBobbly, which is a self-help app delivering content based on acceptance and commitment therapy. The primary outcome for the study is suicidal ideation, and secondary outcomes include depression, hopelessness, distress tolerance, perceived burdensomeness and thwarted belonging, and help-seeking intentions. Data will be collected for both groups at baseline, post-intervention (after 6 weeks of app use), and at 6 months post-baseline (with a final 12-month follow-up for the iBobbly group). Primary analysis will compare changes in suicidal ideation for the intervention condition relative to the wait-list control condition using mixed models. An examination of the cost-effectiveness of the intervention compared to the control condition will be conducted.

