### Secondary aims

The secondary aims are as follows:▪ To test the effectiveness of the iBobbly app compared to a waitlist control condition in reducing levels of suicidal ideation 6 months post-baseline.▪ To test the effectiveness of the iBobbly app compared with the control condition for reducing symptoms of depression, hopelessness, perceived burdensomeness, and thwarted belongingness and for increasing quality of life, help-seeking intentions, and healthcare utilisation immediately post-intervention (6 weeks), and 6 months post-intervention.▪ To examine the 12-month outcomes for participants randomised to the iBobbly group.

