## Trial hypotheses

In accordance with the above aims, the project is driven by several hypotheses:▪ The iBobbly intervention will result in a reduction of suicidal ideation as measured by the Suicidal Ideation Attributes Scale (SIDAS) relative to the wait list control condition post-intervention (six weeks). The SIDAS is the primary outcome measure.▪ The difference in suicidal ideation (measured by the SIDAS) between intervention and wait list control will be maintained at six months.▪ For participants in the intervention group, reductions in suicidality will be maintained at the 12-month follow-up.▪ The intervention will result in a reduction of reported suicide intent and plans as measured by the Quick Inventory of Depressive Symptomatology (QIDAS) relative to the control group at six weeks post-baseline and at six months.▪ Relative to the wait list control condition, the intervention will lower symptoms of depression at six weeks post- baseline and six months.▪ An increase in quality of life and self-reported help-seeking intentions is expected from baseline to six-month follow-up following use of the app.▪ A reduction in suicidality (as measured by suicidal ideation, suicide plans and capacity to cope with suicide thoughts) will be associated with improvement in depression, improvement in burdensomeness and belongingness, improvement in distress tolerance, and greater program adherence.▪ The cost effectiveness analysis will result in a favourable incremental cost effectiveness ratio for the intervention group relative to the control wait list with an improvement in quality of life, with higher costs associated with use of iBobbly app and treatment seeking, but lower use of crisis health care and social services (such as presentations to emergency department and inpatient units).

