## Methods/design

A two-arm randomised controlled trial (RCT) will be conducted (one active intervention/one 6-month wait list control) using three measurement occasions: baseline, post-intervention (after completing the program at week 6), and follow-up at 6 months after baseline assessment. After community consultation, the waitlist control condition was selected as the only acceptable one to the Aboriginal and Torres Strait Islander communities involved in the trial. A SPIRIT checklist (Additional file 1) was completed to address all necessary items in the trial protocol.

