**Fig. 1 Fig1:**
[figure not shown]
Participant flow through the trial

Participants eligible to take part in the study will be given or emailed the Participant Information Statement, consent form and safety agreement by the site coordinator. Participants will also be asked to complete the participant contact form for us to be able to contact the participant at each follow-up point.

All participants will be administered the baseline measures, with those randomised to the intervention group given a mobile tablet device loaded with the app and provided with basic training on how to use it, as well as assistance with setting up their personal identification number. Participants in the wait list control condition will be given the mobile tablet and app 6 months after the intervention group. Active participants will be contacted every 3 weeks until the end of the intervention period, and waitlist participants every 4 weeks, via email or telephone for a wellbeing check. Participants in each group will be provided with information about suicide prevention services and mental health services. This involves direct access to suicide prevention crisis support, and referral to medical providers, if sought or if flagged as at-risk during wellbeing checks. In this instance, an Indigenous psychologist or counsellor will contact the participant and provide triage to local services or engage emergency services where required. Following community consultation it was decided that participant retention be supported through regular contact with the study team, and through a $20 gift card reimbursement for completing each assessment. All participants were free to withdraw from the study at any time.

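### The Analysis plan rules out an untreated comparison at 6 months, but the stated design keeps the wait-list arm without the app until then and the aims call for that comparison

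*Protocol article*

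**What the plan says.** The Analysis plan first sets out the mixed-model comparison at 6 weeks. It then announces separate analyses that bring in the 6-month follow-up. Of that stage it says that change in the active arm can be estimated, and "also to estimate change in the wait-list group after use of the app; however, comparison with an untreated sample will not be possible".

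Other sections of the protocol article describe the 6-month point differently:

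- Methods/design calls the trial "one active intervention/one 6-month wait list control", with the last of three measurement occasions being "follow-up at 6 months after baseline assessment".
- Procedure: "Participants in the wait list control condition will be given the mobile tablet and app 6 months after the intervention group".
- Secondary aims: "To test the effectiveness of the iBobbly app compared to a waitlist control condition in reducing levels of suicidal ideation 6 months post-baseline".
- Trial hypotheses: "The difference in suicidal ideation (measured by the SIDAS) between intervention and wait list control will be maintained at six months". Depression and suicide intent and plans also have hypotheses relative to control at six months.
- Background lists a 6-month between-group follow-up, and a 12-month follow-up within the intervention group, among the changes from the pilot.
- The Abstract describes data collection for both groups to 6 months, "with a final 12-month follow-up for the iBobbly group".

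**The concern.** The Analysis plan is where an analyst looks to learn which contrast to fit. For the 6-month data it says the controlled contrast cannot be had and offers change within each arm instead. The aims and hypotheses ask for the controlled contrast at that same time.

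The two are not interchangeable. A between-arm difference at 6 months is protected by randomisation. Change within an arm mixes any effect of the app with regression to the mean, natural recovery, and the usual care and wellbeing checks that both arms receive. With both statements in the published protocol, either analysis could later be defended as the planned one.

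**Working it through.** This is a conflict of text, so the check is a timeline for the wait-list arm.

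1. **When controls get the app.** Procedure gives it to them 6 months after the intervention group, which receives it at the start. Access therefore begins at about month 6, which agrees with the 6-month wait-list in Methods/design.
2. **When controls are assessed.** Methods/design gives baseline, week 6 and month 6. The later visit, at 12 months, is described in the Abstract and in Community consultation as one for the iBobbly group.
3. **Exposure at the month-6 assessment.** The assessment is at month 6 and access starts at about month 6. On the stated design, the controls have not used the app when they are assessed.
4. **Assessments of controls after app use.** The text describes none.

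Each half of the sentence can now be set against the timeline:

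- *Wait-list change after app use can be estimated.* This needs at least one assessment of controls after month 6, and none is described.
- *Comparison with an untreated sample is not possible.* This would be true if controls had the app before month 6. On steps 1 to 3 they have not.

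The sentence would fit a short wait-list such as the pilot's, described in Background as 6 weeks of waiting followed by 6 weeks with the app. That it was carried over from there is an inference, and the contradiction does not depend on it.

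**A smaller timing conflict.** Secondary aims dates the other outcomes "immediately post-intervention (6 weeks), and 6 months post-intervention". Six weeks is 42 days, and 42 / 30.4 ≈ 1.4 months, so that wording points to about 6 + 1.4 = 7.4 months after baseline. No visit is described then, and Methods/design places the visit at 6 months after baseline. This is a wording slip to reconcile and adds nothing to the size of the main point.

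**The protocol's own sample size.** It reproduces, for week 6 only. With correlation 0.5 the SD of change is √(2 × (1 − 0.5)) = 1 in units of the outcome SD. For d = 0.28, two-sided alpha 0.05 and power 0.80, the t-test calculation gives 201.2, hence 202 complete per arm (power 0.803 with 202). Then 202 / 0.70 = 288.6, hence 289 randomised per arm. Sample size and power calculations ties these inputs to the 6-week time point.

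**The case against.** The best defence is that one sentence does not undo the design. Both arms are assessed at 6 months whatever the Analysis plan says, so the randomised data will exist. The between-arm intent is stated in Background, Secondary aims and Trial hypotheses. The Analysis plan itself says that analyses of secondary measures will assess differential change by arm. This stands as a limit on the size of the problem. A reader might infer that the whole controlled 6-month answer is lost; the documents do not support that. They show a misdirected secondary analysis that can be put right in the text.

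Other readings that go too far:

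- *There will be no wait-list observations at all after app use.* The text describes none, but Figs. 1 and 2 are not shown, so that is as far as it can be put.
- *Every 6-month secondary outcome loses a randomised test.* Trial hypotheses words quality of life and help-seeking as an increase from baseline following app use, which is a within-group statement, although Secondary aims sets them against control.
- *The 6-month test would have 80% power.* The protocol gives no 6-month attrition, correlation or effect size. As illustration only, keep d = 0.28, 289 per arm and the change-score formula. Assumed drop-out of 40% with correlation 0.5 gives power 0.74; 30% with 0.3 gives 0.66; 40% with 0.4 gives 0.66. No 6-month power figure should be claimed.

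Two attempts to rescue the sentence fail. Reading its stage as some time after 6 months does not help, because no later wait-list assessment is described. Reading untreated as having no care at all would be literally fair, since controls have usual care and wellbeing checks, but it leaves the reference to wait-list change after app use unexplained.

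Nor can this be left to a statistical analysis plan that is not shown. The protocol article makes a statement that conflicts with its own design; it does not merely omit detail.

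**Conclusion.** The sentence is wrong as written when set against the design in the same document. On that design the 6-month comparison with an app-free randomised arm is possible, and the alternative estimate has no described data source. If the sentence were followed, the 6-month secondary test of SIDAS, and of the other outcomes with between-arm aims, would become uncontrolled within-arm change. The primary test at 6 weeks is untouched.

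The conclusion assumes that app access for controls starts no earlier than their 6-month assessment, as Methods/design and Procedure imply, and that the missing figures do not show a later wait-list assessment. Untreated here means without the app. The correction is needed because a stated secondary aim depends on it.

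**What to change.** Reconcile the Analysis plan with Background, Secondary aims, Trial hypotheses, Methods/design and Procedure.

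- **If controls are app-free through the 6-month assessment:** replace the sentence with the randomised between-arm contrast in change from baseline to 6 months, using the mixed-model approach already planned, for SIDAS and the secondary outcomes that have between-arm aims. Delete the statement on wait-list change after app use unless such an assessment exists. Limit within-arm analysis to the iBobbly 12-month data.
- **If controls are not app-free to that point:** change the 6-month aims and hypotheses instead, together with the design statements that imply they are.
- **In either case:** reconcile the post-intervention dating in Secondary aims with the post-baseline dating in Methods/design.

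A single model for all three occasions is one way to obtain the contrast, but the correction does not require it.

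The cost is wording in the protocol and any analysis plan, with no new data or visits. The change should be dated and made before 6-month results by arm are seen, so that the choice of contrast cannot appear to follow the data.
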